## Abstract

**Background:**

Frailty is clinically associated with multiple adverse outcomes, including reduced quality of life and functioning, falls, hospitalisations, moves to long-term care and mortality. Health services commonly focus on the frailest, with highest levels of need. However, evidence suggests that frailty is likely to be more reversible in people who are less frail. Evidence is emerging on what interventions may help prevent or reduce frailty, such as resistance exercises and multi-component interventions, but few interventions are based on behaviour change theory. There is little evidence of cost-effectiveness.

Previously, we co-designed a new behaviour change health promotion intervention (“HomeHealth”) to support people with mild frailty. HomeHealth is delivered by trained voluntary sector support workers over six months who support older people to work on self-identified goals to maintain their independence, such as strength and balance exercises, nutrition, mood and enhancing social engagement. The service was well received in our feasibility randomised controlled trial and showed promising effects upon outcomes.

**Aim:**

To test the clinical and cost-effectiveness of the HomeHealth intervention on maintaining independence in older people with mild frailty in comparison to treatment as usual (TAU).

**Methods:**

Single-blind individually randomised controlled trial comparing the HomeHealth intervention to TAU. We will recruit 386 participants from general practices and the community across three English regions. Participants are included if they are community-dwelling, aged 65 + , with mild frailty according to the Clinical Frailty Scale. Participants will be randomised 1:1 to receive HomeHealth or TAU for 6 months. The primary outcome is independence in activities of daily living (modified Barthel Index) at 12 months. Secondary outcomes include instrumental activities of daily living, quality of life, frailty, wellbeing, psychological distress, loneliness, cognition, capability, falls, carer burden, service use, costs and mortality. Outcomes will be analysed using linear mixed models, controlling for baseline Barthel score and site. A health economic analysis and embedded mixed-methods process evaluation will be conducted.

**Discussion:**

This trial will provide definitive evidence on the effectiveness and cost-effectiveness of a home-based, individualised intervention to maintain independence in older people with mild frailty in comparison to TAU, that could be implemented at scale if effective.

**Trial registration:**

ISRCTN, ISRCTN54268283. Registered 06/04/2020.

**Supplementary Information:**

The online version contains supplementary material available at 10.1186/s12877-022-03160-x.

## Background

Frailty is clinically defined as an accumulation of multiple deficits and a reduction in physiological reserves occurring across multiple body systems as we age, leading to poor recovery from even minor events, such as a urinary tract infection or non-injurious fall [1]. Frailty occurs in approximately 12% of people aged 65 + years worldwide [2] and 14% of older people in England [3]. It is associated with an increased risk of falls, disability, hospitalisation, moves to a care home, dementia, poor quality of life and death [4–7]. Healthcare costs are consistently estimated to be higher in frail older people compared to non-frail older people, largely as a result of increased inpatient costs [8–10]. However, frailty can be understood as a continuum and reversal is possible [11].

Exercise programmes, particularly resistance exercise and in combination with nutrition interventions, can reduce frailty in primary care settings [12]. Current international clinical practice recommendations for frailty support the use of a range of interventions, including: physical activity programmes based on resistance training; social support; development of comprehensive care plans addressing polypharmacy, sarcopenia, treatable causes of weight loss and fatigue; and protein or caloric supplementation if the person has lost weight or has evidence of malnutrition [13]. Pharmacological treatments, vitamin D (unless the person is deficient), psychological therapies or hormone therapy are not currently recommended to treat frailty [13].

Frailty is most commonly conceptualised using the Fried phenotype [14] or Rockwood scale [15]. The Fried criteria groups people experiencing more than three of five possible frailty components as ‘frail’, and those with one or two components as ‘pre-frail’ [14]. Pre-frailty is a risk-state which predisposes an individual to developing frailty [16]. The Rockwood scale classifies people from robust to severely frail, using either cumulative deficits or clinical observation [15]. There is a wide range of differences in functioning across the spectrum of frailty, and little guidance on where to target interventions, although a meta-analysis of 16 studies suggested that over an average of 3.9 years, those who are frail (using the Fried phenotype) are less likely to transition back to robustness than those who are less frail [11]. This suggests targeting earlier stages of frailty is likely to be a more successful approach to preventing decline.

Mild frailty is an intermediate stage on the Rockwood Clinical Frailty Scale where older people experience some loss of physiological reserves but can recover after a stressor event, typically feeling “slowed up”, and requiring greater assistance in instrumental activities of daily living, e.g. cooking, shopping and money management [15]. Around 13% of older people can be classed as ‘mildly frail’ [15]. Mild frailty is associated with adverse outcomes, including a higher risk of death and moving into a care home [15], increased need for care at discharge from hospital [17] and poorer outcomes after post-surgical discharge [18]. Few interventional studies have targeted a mildly frail population with the aim of maintaining independence.

There is little focus in clinical guidelines on frailty prevention, apart from a brief reference to the use of exercise in pre-frailty to prevent frailty [13]. Few UK policies are directed ‘upstream’ to those who are less frail [12], although England’s NHS Long-Term Plan [19] clearly emphasises prevention and ‘supporting people to age well’, including proactively identifying those who would benefit from targeted support to maintain independence. Most studies on frailty prevention (generally targeting those who are pre-frail) have focussed on single or dual intervention domains, typically exercise plus or minus nutrition [20, 21]. Multi-domain interventions including exercise and a range of other domains such as social, nutritional, cognitive training, or medication review show greater promise at reducing or preventing frailty and its related domains across a number of trials [22–25].

However, there is a lack of clarity on which strategies need to be adopted within interventions to maximise effectiveness, as well as absence of a clear theoretical basis, rigorous development process or stakeholder input in intervention development [26]. This can provide challenges when optimising or implementing interventions. Very limited evidence suggests group-based exercise interventions may be more effective than individual sessions, however this may not be feasible to deliver to those who are finding leaving their home more challenging, and there is currently little guidance as to the optimal frequency, intensity, time and type of exercise interventions for frailty management or prevention [13]. More holistic approaches, such as comprehensive geriatric assessment with follow-up visits or preventative home visits, are promising [27, 28] but typically resource-intensive, requiring nurses or a multidisciplinary team, and so present challenges to delivery at scale. The limited number of cost-effectiveness studies available at present showed mixed results. Multidisciplinary team meetings with proactive care management across multiple domains targeted at frail older people, such as The CareWell programme or the Welcheren Integrated Care model, have not shown cost-effectiveness compared to usual primary care [29, 30]. However a resistance training and nutrition education intervention for pre-frail and frail older people with diabetes produced cost savings and increased QALYs [31], whilst a cognitive behavioural intervention to reduce concerns about falls in frail older people was found to be cost-effective [32].

In response to these gaps in the evidence, in an earlier study we developed and feasibility tested an intervention to support independence in older people with mild frailty [33], following Medical Research Council guidelines [34]. The HomeHealth service is a complex theory- and evidence-based behaviour change intervention, arising from an asset-based approach [35], Baltes’ model of ageing [36] and behaviour change theory [37]. Asset-based approaches aim to maximise positive capability and maintain health promoting factors to enhance self-efficacy, problem-solving and coping, in order to retain reserves and functioning [35]. This contrasts to the more commonly used deficit-based approach, which focuses on individuals’ problems and what they lack. Baltes’ model of ageing suggests that successful ageing occurs when an older person prioritises realistic goals or activities that they want to maintain (selection), optimises how these can be performed (optimisation) and adjusts for limitations (compensation) [36]. The behaviour change theory component is based upon the COM-B model, which states that for any behaviour to take place, the person must have sufficient physical and psychological capability, social and physical opportunity and conscious or innate motivation [37]. COM-B provides a framework to link these factors to the specific techniques needed to enable changes in behaviour.

The HomeHealth service is a home-based intervention that we developed based on a series of evidence reviews regarding intervention content and behaviour change techniques used in health promotion interventions for older people [26, 33, 38] and qualitative research with older people with mild frailty, carers and healthcare professionals [39]. It was then co-designed with a range of stakeholders, including older people, healthcare professionals, researchers and voluntary sector representatives [33].

The HomeHealth service was tested in a feasibility randomised controlled trial (RCT) compared to treatment as usual (TAU, usual GP care), in which we recruited 51 older people with mild frailty from four UK general practices, 26 of whom received the intervention. The study successfully recruited within the expected timeframe, with 96% participants remaining in the study at 6 months and minimal missing data (< 1%) [33]. Our process evaluation indicated that the intervention was well-received according to participant interviews and a survey [40], feasible to deliver and had 91% attendance rates for appointments. The service was delivered at modest cost (£307—equivalent $417/patient in Feb 2022). At 6 months we found significantly better functioning (Barthel Index; + 1.68, p = 0.004) and grip strength (+ 6.48 kg, p = 0.02), reduced psychological distress (GHQ-12; -3.92, p = 0.01) and increased capability-adjusted life years (+ 0.017, p = 0.03) in the intervention arm compared to treatment as usual. There were no differences in other outcomes. Given the promising nature of the intervention, we aim to test the effectiveness and cost-effectiveness of HomeHealth in a definitive trial across a wider range of participants, providers and contexts.

### Aims

This trial aims to:Test the clinical effectiveness of HomeHealth in maintaining independence in a RCT in comparison to TAU.Determine the cost-effectiveness of HomeHealth in comparison to TAU.Quantify the costs and savings of HomeHealth to different health and social care providers.Explore the context, mechanisms and impact of the intervention for different populations (age, gender, deprivation, ethnicity, rurality) and barriers and facilitators to implementation at scale.

## Methods

We will carry out a two-arm, single-blind, parallel-group RCT comparing HomeHealth to TAU, including a cost-effectiveness analysis and mixed methods process evaluation.

### Eligibility criteria

We will include community-dwelling older people (including those in sheltered or extra care housing – no care workers on site) aged 65 + who are registered with a general practice in the participating site area; scoring as ‘mildly frail’ on the Clinical Frailty Scale (CFS score of 5), which is defined as ‘more evident slowing, who need help or support in higher order instrumental activities of daily living (e.g. finances, heavy housework), with progressive impairment of outdoor mobility, shopping and housework’ [15]; life expectancy of > 6 months; and capacity to consent to participate.

We will exclude care home residents; people with moderate-severe frailty (CFS score of 6–9) or not frail (CFS score of 1–4); receiving palliative care; or already case managed (e.g. receiving a similar ongoing intervention from the voluntary sector or a community matron).

### Intervention

A detailed breakdown of the HomeHealth service is provided according to the TIDIER checklist [41] in supplementary file 1. HomeHealth is delivered over approximately six appointments in the older person’s home. Three appointments is considered a minimum dose, whilst participants could receive up to a maximum of 12 if they have particularly complex needs. These were originally planned to be delivered face-to-face with some telephone interim support, however they were adapted to be delivered by phone or video call, as needed, in light of the Covid-19 pandemic. If needed, internet-enabled tablets can be offered to participants receiving the intervention remotely to facilitate communication.

HomeHealth follows an intervention manual. In the first appointment, a HomeHealth worker comprehensively assesses the person, with a particular focus on socialising, mobility, nutrition and psychological wellbeing (including mood and memory), but including any other relevant issues (e.g. pain, continence, caring). Participants are encouraged to identify an outcome goal for the service that is important for them, and at either the first or second appointment are encouraged to break this down into behavioural goals, which are then operationalised into SMART (specific, measurable, achievable, relevant, timely) goals that are achievable in small steps over the course of the intervention. Goals can include a range of activities, such as home-based exercises based on the Otago programme (which shows effectiveness at reducing falls [42] and improving balance [43]), identifying social activities to attend or making dietary changes to improve protein or calorie intake. The COM-B model [37] is used by the HomeHealth worker to assess capability, opportunity and motivation to achieve the behavioural goal and to identify any barriers, developing an action plan with the person as to how these might be overcome. These are documented on a Health and Wellbeing Plan, and self-monitoring forms (e.g. diaries) may be used to record completion of activities such as exercises. Where relevant, equipment (e.g. weights or resistance bands) or information resources (e.g. details of local social groups) is provided to the older person.

At each subsequent appointment, progress towards achieving goals is reviewed, with changes made as needed to resolve any issues or to extend goals (e.g. increasing repetitions or resistance in strength exercises). An emphasis is placed on how new behaviours could be maintained over time, and habit formation. Further goals may be identified over following sessions. There are no restrictions on accessing other services or treatments during the study period.

HomeHealth is delivered by trained HomeHealth workers, who are not required to have a specific health or social care qualification but to have some experience in working with older people (for example, in the voluntary or not for profit sector). HomeHealth workers are based in local voluntary sector services in each area and are supervised by a centrally located Team Leader, in biweekly remote group supervisions with one-to-one support as needed. HomeHealth training is delivered entirely remotely as a blend of live and asynchronous content delivered by specialists in that area, including pre-recorded webinars and live seminars, activities and a strong emphasis on case-based discussions. The training time is intended to be equivalent to a one-week course. HomeHealth workers also have access to remote support from the expert course providers (in behaviour change, exercise for older people, nutrition and psychological wellbeing) via email for specific queries on tailoring the intervention for individual clients.

The control arm will receive TAU. This is defined as standard care that any eligible patient aged 65 + would normally receive in England in primary care (e.g. contact with the GP or the practice nurse), including any other community or secondary care input as a result of referral by a GP. No mild frailty-specific interventions are currently widely available in the UK.

### Setting and recruitment

Participants will be recruited from general practices in England, in one of three areas (North Thames Region, East & North Hertfordshire and West Yorkshire). Practices will be asked to undertake list searches to identify those fitting the eligibility criteria above, using the frailty tool available to the practice (usually the Electronic Frailty Index) [44], which will then be screened by clinicians to remove known ineligible patients. Practices will then send invitation letters, study leaflets and reply slips to potentially eligible patients. Potential participants can also be referred to the study directly by clinicians in participating General Practices or local voluntary sector staff. We will undertake community-based recruitment such as presenting to local groups and providing leaflets to relevant community organisations, targeting under-served populations to maximise diversity of our sample.

Researchers will telephone screen potential participants according to the inclusion criteria, and if eligible, will post an information sheet and invite them to an appointment (face-to-face or remote) to seek consent and undertake a baseline assessment. An interpretation service is available if required. After completion of a baseline assessment and confirmation of eligibility, participants will be randomised.

### Randomisation

We will randomise participants 1:1 (stratified by site) to receive the HomeHealth service or TAU. Randomisation will be carried out by unblinded staff members using the remote computerised web-based application ‘Sealed Envelope’, provided by UCL's Priment Clinical Trials Unit. Outcome assessors, the Chief Investigator, the Trial Manager and Trial Management Group members who are not site Principal Investigators or responsible for intervention delivery will be blinded to participant allocation.

### Outcomes

Clinical outcomes will be measured at baseline, 6 months and 12 months by a researcher blind to intervention status (see Table 1). Maintenance of blinding will be documented using a Researcher Perception form. Assessments will be completed face-to-face at the participant’s home or remotely (by video or telephone), according to any government guidelines for prevention of Covid-19 infection and the participant’s preferences. Assessments can be divided into two sessions if needed. Participants receive a £10 voucher (max 3) for completing each assessment. Data will be kept confidentially at sites and entered in a secure web-based database developed for the trial. A monitoring plan is in place to ensure data quality.

**Table 1 Tab1:** List of data collected and timepoints

Construct	Measure used (supporting references)	Baseline	6 months	12 months	Anytime	Extracted from medical notes
Independence in ADLs	Modified Barthel Index [45]	✓	✓	✓		
Instrumental ADLs	Nottingham Extended Activities of Daily Living [46]	✓	✓	✓		
Frailty	Fried Frailty Phenotype score [14]	✓	✓	✓		
a.Gait speed	Self-reported according to Op het Vald’s (2018) questionnaire [47]	✓	✓	✓		
b. Grip strength	Self-reported according to Op het Vald’s (2018) questionnaire [47]	✓	✓	✓		
c. Physical activity	International Physical Activity Questionnaire-Elderly [48], quantified according to the E guidelines [49]	✓	✓	✓		
d. Exhaustion	Exhaustion questions from 7-item Centre for Epidemiological Studies Depression Scale “7. I felt that everything I did was an effort,” “20. I could not get going.” [14]	✓	✓	✓		
e. Weight loss	Weight loss question from the Mini-Nutritional Assessment Short Form [50]	✓	✓	✓		
Quality of life and Quality-adjusted Life Years	EuroQol-5D-5L [51]	✓	✓	✓		
Capability and Capability-adjusted Life Years	ICEpop CAPability measure for Older people (ICECAP-O) [52]	✓	✓	✓		
Wellbeing	Warwick-Edinburgh Mental Wellbeing Scale (WEMWBS) [53]	✓	✓	✓		
Psychological distress	General Health Questionnaire-12 [54]	✓	✓	✓		
Loneliness	University of California, Los Angeles 3-item loneliness scale [55]	✓	✓	✓		
Cognition	Montreal Cognitive Assessment (MoCA) [56] or telephone MoCA (remote items only) [57, 58]	✓	✓	✓		
Falls	ProFANE consensus definition [59]	✓	✓	✓		
Mortality	Medical notes or family report		✓	✓	✓	
Carer burden	Adapted from adapted iMTA Valuation of Informal Care Questionnaire [60]	✓	✓	✓		
Demographics	Questionnaire developed for trial	✓				
Alcohol intake	Alcohol Use Disorders Identification Test – consumption (AUDIT-C [61])	✓				
Deprivation level	Local area Index of Multiple Deprivation based on postcode [62]	✓				
Smoking status	Single question	✓				
Covid-19 status	Questions on infection status and ongoing symptoms	✓	✓	✓		
Unpaid care and use of primary and community health and social care services	Modified Client Services Receipt Inventory [63]	✓	✓	✓		
Use of health services, medications and number of long-term conditions						✓
Adverse events			✓	✓	✓	✓

The primary outcome is the Modified Barthel Index (BI) [45] measured at 12 months, which is interviewer-administered with scoring based on discussions with participants. The BI measures an individual’s ability to undertake basic Activities of Daily Living (ADLs) and is widely used, correlates well with need for home care [64] and is considered a key outcome measure in frailty trials [65]. It measures what people actually do as opposed to what they could do. Our intervention arm showed significantly higher scores than usual care in our feasibility RCT at 6 months [33]. Our secondary outcomes and variables collected at each timepoint are reported in Table 1.

The study was planned before Covid-19 (winter 2019) and we intended to conduct face-to-face research assessments, measuring frailty using handgrip strength (dynamometer), gait speed (time taken to walk a measured distance) and weight loss (measured using scales). Given the restrictions associated with the pandemic that were implemented in March 2020, we revised our protocol to use self-report measures (validated in older people across a range of frailty levels [47]) to enable remote assessments. When research assessments are conducted face-to-face, we will additionally carry out physical gait speed assessment (m/s) [66] and grip strength assessment using a dynamometer (kg, highest score out of three trials) [67] to confirm the validity of the self-report measures in our population with mild frailty.

### Safety

Researchers will collect Adverse Events (AEs) and Serious Adverse Events (SAEs) at 6-and 12-month timepoints, and participants will be encouraged to report any AEs or SAEs experienced between assessments by contacting researchers. HomeHealth workers (HHWs) will also report adverse events. All AEs and SAEs will be reviewed by a site Principal Investigator and/or Clinical Safety Lead (CSL), and all SAEs will be reviewed by the Chief Investigator. Only SAEs related to the intervention will be reported to the Sponsor. Researchers will not have access to relatedness assessments in order to maintain blinding. Relatedness to the intervention will be assessed by the site Principal Investigator and/or CSL in a blinded manner for AEs and SAEs reported by researchers, and unblinded for AEs and SAEs reported by HHWs. The reporting of SAEs will be monitored by Priment CTU. Pharmacovigilance standard operating procedures will be followed.

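### Adverse events have an extra reporting route in the HomeHealth arm only, and the SAE review does not fit the stated blinding of the Chief Investigator

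*Protocol article*

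**What the plan says.** **Collection.** The Safety section of the protocol article gives two routes open to everyone. The scheduled one is "Researchers will collect Adverse Events (AEs) and Serious Adverse Events (SAEs) at 6-and 12-month timepoints"; between visits, "participants will be encouraged to report any AEs or SAEs experienced between assessments by contacting researchers". In Table 1 the row "Adverse events" is ticked at 6 months, 12 months, anytime and for extraction from medical notes, with no limit to one arm. Safety then adds a further route: "HomeHealth workers (HHWs) will also report adverse events".

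**Who the workers see.** Under Intervention, "HomeHealth is delivered over approximately six appointments", with three as the minimum dose and 12 as the maximum. The control arm receives usual care and has no HomeHealth worker.

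**Relatedness.** The site Principal Investigator and/or the Clinical Safety Lead judges relatedness "in a blinded manner for AEs and SAEs reported by researchers, and unblinded for AEs and SAEs reported by HHWs". Only SAEs judged related go to the Sponsor. Researchers do not see these judgements.

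**Blinding.** In Randomisation, the list of blinded roles opens with the outcome assessors and the Chief Investigator and continues: "the Trial Manager and Trial Management Group members who are not site Principal Investigators or responsible for intervention delivery will be blinded". In Safety, "all SAEs will be reviewed by the Chief Investigator", with no exception and no masking step described.

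**The concern.** Two separate matters are at stake.

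The first is ascertainment. An event in the intervention arm has one more way of reaching the database than the same event in the control arm. Minor events that never reach a GP, and that may be forgotten by the six-month assessment, are the kind a home visitor hears about. If by-arm AE or SAE counts are pooled over all sources, HomeHealth can look less safe because it was watched more closely. The Data Monitoring and Ethics Committee reviews all safety data, so it too could be shown such counts.

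The second is blinding. The Limitations section relies on blinding assessors and key trial management staff to reduce bias. An SAE reported by a HomeHealth worker identifies the participant's arm by its source. As written, a Chief Investigator who reviews every SAE receives those reports too. The same roles are also given both the unblinded and the blinded relatedness judgements. An analysis plan could separate the sources later only if the source had been recorded, and it cannot restore blinding already lost.

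**Working it through.** **Figures in the plan.** The article states no AE rate, capture rate or AE comparison, so there is no safety figure to reproduce. Its sample size does reproduce: 2 × (1.960 + 1.282)² × 5² / 1.85² = 153.5, so 154 per arm and 308 in all; 154 / 0.80 = 192.5, so 193 per arm and 386 in all. It plays no part in this point.

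**Sources by arm.**

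| Source | HomeHealth | Usual care |
|---|---|---|
| Researcher at 6 and 12 months | yes | yes |
| Participant report between visits | yes | yes |
| Medical notes (with consent) | yes | yes |
| HomeHealth worker | yes | no |

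Scheduled occasions on which someone may learn of an event number 2 in usual care, against 2 + 6 = 8 under HomeHealth, or up to 2 + 12 = 14. This count leaves out participant reports and note extraction, so it overstates the gap in information. An added source can only add recorded events, which fixes the direction.

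**Possible size (assumed inputs).** Let the true risk p be equal in both arms. Let s be the share of participants with an event who are captured by the common sources, and h the share of the remainder found only through workers. Then:

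- recorded risk, usual care: p·s
- recorded risk, HomeHealth: p·[s + (1 − s)·h]
- recorded risk ratio: 1 + h·(1 − s)/s, which does not depend on p

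| s | h = 0 | h = 0.25 | h = 0.50 |
|---|---|---|---|
| 0.50 | 1.00 | 1.25 | 1.50 |
| 0.70 | 1.00 | 1.11 | 1.21 |
| 0.90 | 1.00 | 1.03 | 1.06 |

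For example, at s = 0.70 and h = 0.25: 1 + 0.25 × 0.30 / 0.70 = 1.107.

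Workers are in contact for six of the twelve months. If missed events are spread evenly over the year, h = 0.25 means that workers find half of those falling in their six months (0.5 × 0.5), and h = 0.50 means that they find all of them. On that assumption the right-hand column is a ceiling for each s.

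**Blinding, section against section.**

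1. Chief Investigator: Randomisation says blinded. Safety says reviews all SAEs. All SAEs include worker-reported ones, and a worker report exists only for an intervention participant. Without masking of the source, both statements cannot hold.
2. Relatedness assessor: Safety gives worker reports and researcher reports to the same roles. Someone who has seen a worker report on a participant knows that participant's arm and cannot judge a later researcher report on the same participant blind. Nothing in the text keeps the two streams apart.

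**The case against.** The strongest reply is that the article specifies no between-arm test of AEs. Statistical methods names models for the Barthel Index, the continuous secondary outcomes, death, exhaustion and falls. Falls and mortality follow a Table 1 schedule common to both arms. How AEs are tabulated is normal content for the analysis plan, which is announced but not shown. Medical notes also cover both arms, hospitalisations are extracted from records, and the six-month assessment falls at the end of the intervention period, so worker reports may only duplicate what is already known. All of this stands. A reader might infer that the safety comparison is already biased, or that an excess is bound to appear. The documents show only that a pooled count is exposed to such an excess, and any percentage put on it rests on assumed inputs.

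A reader might also infer that rates of related events ought to be comparable between arms and are spoiled by the two modes of assessment. That does not follow. Relatedness is to HomeHealth, which usual-care participants do not receive, so no wording would make those rates comparable.

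Nor does the Safety section contradict itself over relatedness: it discloses both modes openly and keeps the judgements from the researchers who assess outcomes. It is likewise tempting to say that site Principal Investigators, who are left out of the blinded group, cannot assess blind. That is the weaker part, because the phrase can describe how a report is presented, and a blinded researcher's report need not carry the arm. What survives is narrower: prior sight of a worker report on the same participant.

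Finally, standard operating procedures might mask reports before the Chief Investigator sees them. The article refers to such procedures but describes no masking, so the two sections still need reconciling.

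**Conclusion.** The point holds in a limited form. One reporting route exists in the intervention arm only, and by-arm AE or SAE counts pooled over all sources are open to excess recording under HomeHealth. The direction is certain and the size is not. With equal true risks, common sources capturing 50% to 90% of affected participants, and workers finding none to half of the rest, the recorded ratio lies between 1.00 and 1.50. None of these capture rates comes from the documents.

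The Randomisation and Safety sections also disagree on the Chief Investigator, and the arrangement for relatedness does not protect the assessment that is called blinded. The documents do not show that the Chief Investigator has in fact been unblinded, or that any efficacy result is affected. The Barthel analysis, the sample size and the blinding of outcome assessors are untouched.

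**What to change.** 1. Record the reporting source or sources of every AE and SAE on the event form.
2. State that the between-arm comparison of AEs and SAEs uses only sources common to both arms: researcher collection at 6 and 12 months, participant reports and medical notes.
3. List events known only from HomeHealth workers separately for the intervention arm, and give the Data Monitoring and Ethics Committee both displays. All events, whatever their source, are still reviewed for safety.
4. Reconcile Randomisation with Safety by masking source and arm before the Chief Investigator's review of SAEs.
5. Have researcher-reported events assessed for relatedness by someone who does not handle worker reports on that participant. The present wording, site Principal Investigator and/or Clinical Safety Lead, leaves room for this. If it is not practicable, stop describing that assessment as blinded.

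The cost is one form field, a masking step for SAE reports, a few sentences in the protocol and analysis plan, and slightly fewer events in the comparative table. No visits are added.
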